#### Statistical analysis

2.10.16

The data will be analyzed via SPSS version 25. The normality of the data will be assessed with the Kolmogorov‒Smirnov test. Descriptive statistics will include the mean ± SD for normally distributed variables and the interquartile range (IQR) for nonnormally distributed variables. Pre- and postintervention measures will be compared using a paired *t*-test, whereas frequency tables and medians will describe categorical and continuous data. Categorical variables will be analyzed via the chi-square test or Fisher's exact test, and continuous variables will be analyzed via the Mann‒Whitney *U* test. Survival analysis (Kaplan‒Meier and Cox regression) will be used for time‒to‒event outcomes, and ANCOVA will compare primary outcomes at baseline, day 5, and day 10. Potential confounders including age, sex, BMI, APACHE II score at ICU admission, admission diagnosis category, vasopressor use during the intervention, and predefined comorbidity groups will be included as covariates in multivariable regression and ANCOVA models. These adjusted analyses will be applied to both primary (zonulin levels) and secondary outcomes where appropriate to minimize residual confounding. Longitudinal regression models will assess the intervention's effect, controlling for the same confounding factors. Statistical significance will be set at p < 0.05.

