### Trial design

2.1

This study is a randomized, double-blind clinical trial with two groups that receive different doses of protein via enteral nutrition: the CP group and the HP group. All patients will received enteral nutrition through tube feeding. Critically ill patients admitted to the ICU will be eligible for enrollment 24 h after admission. Protein administration begins 48 to 72 h after admission, depending on the patients' suitability. The acute physiology and chronic health evaluation II (APACHE II) and modified nutritional risk in critically ill (mNUTRIC) scores will be assessed at ICU admission. Sequential Organ Failure Assessment (SOFA) score will be evaluated at the beginning and end of the intervention period. Blood samples will be collected on days 0, 5, and 10 for the measurement of zonulin levels and intestinal permeability. Serum zonulin has been widely used in clinical studies as a practical and minimally invasive biomarker reflecting intestinal barrier function [22]. Established tests for intestinal permeability, such as the lactulose/mannitol ratio, are limited in critically ill ICU patients due to practical and clinical constraints, including the need for enteral substrate administration, timed urine collection, and potential hemodynamic instability [23]. Therefore, we used serum Zonulin as a reliable biomarker for intestinal barrier function in ICU patients. [13,21,22,24]. The medication administered during the intervention will be documented and organized by drug class. During the 10-day intervention, patients will be under continuous clinical observation and full monitoring by the treatment team and will be constantly monitored for protein feeding tolerance. The blood samples will be centrifuged and frozen at −70 °C until laboratory analysis. Finally, data on zonulin levels, intestinal permeability, and clinical scores will be analyzed via SPSS and appropriate statistical methods. The trial procedure is illustrated in the flow chart presented in Fig. 2. The protocol was created following the SPIRIT guidelines (see Table 1).

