#### Secondary objective

2.10.2

The secondary objective was to investigate the effects of HP versus CP in enteral nutrition on illness severity and mortality in critically ill ICU patients.

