## Discussion

3

This study is the first clinical trial that examined the effects of high-protein enteral nutrition on intestinal permeability, disease severity, and mortality in critically ill patients in the ICU. Critically ill ICU-admitted patients are often at risk of sepsis, inflammation, and impaired intestinal barrier function [25]. These patients are also prone to malnutrition and systemic inflammation, which lead to poor outcomes and increased mortality rates [26].

Nutritional support, especially enteral nutrition and protein intake, can effectively improve epithelial barrier function and reduce intestinal permeability in these patients [16].

Zonulin is a membrane protein that plays a role in maintaining tight junctions between intestinal epithelial cells (through binding to proteins such as claudin, occludin, junctional adhesion molecules, and the actin cytoskeleton) and is considered a marker of epithelial barrier function [27]. The production of this protein is usually regulated by inflammatory cytokines such as IL-1, IL-6, and TNF-α and is increased during inflammatory conditions [28].

The gastrointestinal microbiome can also influence the clinical status of critically ill patients [29]. Dysbiosis or an imbalance in the microbiome is associated with increased zonulin secretion, impaired intestinal permeability, and inappropriate regulation of inflammatory mediators [30]. Therefore, enteral nutrition and protein intake can significantly affect the disease process, epithelial barrier function, and intestinal permeability [16].

The SOFA score is a suitable tool for predicting survival and ICU discharge [31,32]. The APACHE II score also estimates the severity of the disease on the basis of data from the first 24 h of hospitalization [33]. The mNUTRIC questionnaire is also used as a screening tool for the risk of severe malnutrition in ICU patients [34,35].

The present study aims to identify a scientific gap by investigating the effects of high protein administration in enteral nutrition on serum zonulin concentrations, severity of illness scores (APACHE II, SOFA), nutritional risk, and mortality in ICU patients. If protein administration causes a significant reduction in zonulin levels and improved clinical outcomes, the results of this trial could influence future guidelines on protein dosing in enteral nutrition in ICU patients [13].

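### The paired t-test planned for pre/post measures, which takes in SOFA, has no arm term and is not limited to description, and start-of-intervention SOFA is missing from the covariates of the between-arm models

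*Protocol article*

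**What the plan says.** The secondary objective (protocol article, 2.10.2) is a comparison of arms: the "effects of HP versus CP in enteral nutrition on illness severity and mortality in critically ill ICU patients". SOFA is a listed secondary outcome (2.10.5). Under Trial design (2.1) the SOFA "score will be evaluated at the beginning and end of the intervention period".

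The Statistical analysis section (2.10.16) names several methods:

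- "Pre- and postintervention measures will be compared using a paired" t-test. No outcome is named, and the text does not say whether the test is run in each arm or in both arms pooled.
- "continuous variables will be analyzed via the" Mann-Whitney U test.
- "ANCOVA will compare primary outcomes at baseline, day 5, and day 10".
- Multivariable regression and ANCOVA with age, sex, BMI, APACHE II at admission, admission diagnosis category, vasopressor use and comorbidity groups as covariates. Of these it says: "These adjusted analyses will be applied to both primary (zonulin levels) and secondary outcomes where appropriate to minimize residual confounding".
- A further class of model, again with no outcome named: "Longitudinal regression models will assess the intervention's effect, controlling for the same confounding factors".

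No sentence names SOFA, says which result decides the SOFA comparison, or calls the paired test descriptive.

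**The concern.** A paired t-test has as its null that the mean change over time is zero. Equal effects of the two protein doses do not make that null true. Recovery, regression to the mean and loss of the sickest patients can move SOFA in both arms alike. The test can therefore reject because time has passed, whatever the dose does. Pooling the arms would not help, since the pooled test has no arm term either.

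What is at stake is how the SOFA result is read. A significant fall in the HP arm, or a fall that is significant in HP but not in CP, could be taken as a benefit of high protein when the doses do not differ. Correcting alpha would not help, because the test answers a different question from the one in the objective.

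**Working it through.** **Step 1: which outcome the paired sentence covers.** Zonulin has three time points and its own ANCOVA sentence. APACHE II and mNUTRIC are scored only at ICU admission (2.8). Mortality and length of stay have no baseline value. SOFA is the one outcome measured exactly once before and once after.

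**Step 2: inputs.** The protocol article gives no expected SOFA change, SD or pre/post correlation, so there is no figure of the plan's own to reproduce. The numbers per arm, 41 before and 44 after the attrition allowance, come from 2.9 and are used only as group sizes. Assumed: no HP-CP difference, the same mean change in both arms, normally distributed changes, two-sided alpha 0.05.

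**Step 3: chance that a within-arm paired test is significant.** Let δ be the shared mean change divided by the SD of the change. The test statistic is noncentral t with n − 1 degrees of freedom and noncentrality λ = δ√n, and p is the probability that it passes the two-sided 5% limits. The arms are independent, so the chance of HP significant and CP not is p(1 − p).

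| n per arm | δ | λ = δ√n | p | p(1 − p) |
|---|---|---|---|---|
| 41 | 0.3 | 1.92 | 0.466 | 0.249 |
| 44 | 0.3 | 1.99 | 0.494 | 0.250 |
| 41 | 0.5 | 3.20 | 0.878 | 0.107 |
| 44 | 0.5 | 3.32 | 0.900 | 0.090 |

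In SOFA points, an assumed shared fall of 1.5 with a change SD of 3 is δ = 1.5/3 = 0.5, the last two rows. With a change SD of 4, δ = 1.5/4 = 0.375 and p is 0.649 (n = 41) or 0.681 (n = 44).

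**Step 4: sensitivity.** If the fall is instead expressed in SDs of the score, the SD of the change is √(2(1 − ρ)) score SDs for pre/post correlation ρ. At n = 44, with falls of 0.2 to 0.8 SD and ρ from 0.3 to 0.7, p runs from 0.20 to nearly 1. The HP-only pattern never exceeds 0.25, the maximum of p(1 − p).

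**Step 5: between-arm tests under the same null.** In 4,000 simulated trials with n = 44, a shared fall of 0.5 SD and ρ = 0.5, ANCOVA on the starting score rejected in 0.046 and Mann-Whitney U in 0.039, while the paired test in the HP arm rejected in 0.901. In 20,000 simulated trials with n = 41 and δ = 0.3, a between-arm t-test rejected in 0.052.

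**Step 6: what the missing covariate costs.** Adjusting for the starting score multiplies the outcome variance by about 1 − ρ². That is 1 − 0.09 = 0.91 at ρ = 0.3, 1 − 0.25 = 0.75 at ρ = 0.5 and 1 − 0.49 = 0.51 at ρ = 0.7, relative to an unadjusted comparison of end scores. The gain would be smaller where APACHE II already explains part of the same variation.

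**The case against.** A reader might infer that the paired t-test is the plan's test of SOFA efficacy, so that the trial's false-positive rate for SOFA is 47% to 90%. The document does not support that. Its only sentence about which method assesses the intervention's effect points to longitudinal regression. Mann-Whitney U is given for continuous variables without restriction; the qualifier about appropriateness applies only to the adjusted models. The objectives are worded as HP versus CP, and the sample size rests on an independent-samples test. The probabilities above become error rates only if someone uses the paired test as the between-arm test, and no sentence says that anyone will.

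Nor does the Discussion supply that sentence. "If protein administration causes a significant reduction in zonulin levels and improved clinical outcomes" attaches significance to zonulin, for which ANCOVA is named, and it is discussion prose, not a decision rule.

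It can also be said that the choice of deciding analysis for a secondary outcome belongs in a statistical analysis plan, which is not shown, and that ANCOVA is often understood to adjust for the baseline value. The first point is fair as far as missing detail goes.

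What remains is what the article does state. It plans a test for pre/post measures that cannot address the objective, subject to the same p < 0.05 rule as the others and with no limit on its use. It also lists the covariates explicitly, and start-of-intervention SOFA is not among them. The longitudinal sentence names no outcome, and the adjusted models reach secondary outcomes only conditionally.

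**Conclusion.** The point holds in a limited form. The paired t-test covers SOFA, cannot answer the HP-versus-CP question, and is not marked as descriptive; the covariate list leaves out the starting SOFA score, which the trial already collects. The plan does contain between-arm analyses, so this is not a trial without a valid SOFA comparison, and its type I error has not been shown to be inflated.

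The 47% to 90% for a significant within-arm result, and the 9% to 25% for HP significant alone, are the chances of a misleading within-arm p-value. They rest on an assumed shared fall of 0.3 to 0.5 SD of the change, normal changes and 41 to 44 patients per arm. A smaller shared change would lower the first figure. Severity is low to moderate: one secondary outcome is affected.

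**What to change.** In 2.10.16, keep the clause on frequency tables and medians and replace only the paired t-test clause with:

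> The effect of HP versus CP on end-of-intervention SOFA will be estimated as the between-arm difference by ANCOVA with start-of-intervention SOFA as a covariate, with 95% CI; within-arm changes will be reported descriptively and will not support conclusions about protein dose.

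This is a change of wording. Both SOFA scores are already collected, no patients or visits are added, and the Trial registration section states that recruitment had not begun. The small downside is that within-arm p-values no longer serve as evidence.

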### Sample size

2.9

The sample size was determined on the basis of serum zonulin levels, which were considered the primary outcome of the study. In the study by Klaus et al. [21], the mean zonulin level in the target patient population was reported to be 3.40 ng/mL, with a standard deviation of 0.71. A type I error (α) of 0.05 and a statistical power (1−β) of 80% were used for the calculation. A 10% change in zonulin levels was deemed clinically significant. This threshold was chosen based on previous reports of variation in zonulin levels in critical illness and feasibility considerations for sample size estimation [21]. The exploratory nature of this outcome is acknowledged. Using the standard formula for sample size estimation based on a two-sided independent samples *t*-test to determine the mean of the intervention group versus the control group, the required sample size was calculated to be 41 participants per group, or a total of 82 participants. The final sample size was adjusted to 44 participants in each group, out of a total of 88 participants, considering an expected attrition rate of 5% during the study period.

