#### Primary outcomes

2.10.4

•Zonulin levels will be measured to assess intestinal permeability.

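### Overlapping zonulin analyses share one 0.05 threshold with no deciding test, none is the t-test used for the sample size, and a pre/post paired test does not compare HP with CP

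*Protocol article*

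**What the plan says.** **Outcome.** Section 2.10.4 gives the primary outcome as "Zonulin levels will be measured to assess intestinal permeability". The abstract gives it as the change in serum zonulin over the intervention period. Samples are taken on days 0, 5 and 10. Neither place names a deciding day or summary measure.

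**Planning.** Section 2.9 states "A type I error (α) of 0.05 and a statistical power" "of 80% were used for the calculation". The test is given as "Using the standard formula for sample size estimation based on a two-sided independent samples" *t*-test. The same section concedes that the outcome is exploratory.

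**Analysis.** Section 2.10.16 lists:
- a paired test: "Pre- and postintervention measures will be compared using a paired" *t*-test, with no outcome named;
- a rank test: "continuous variables will be analyzed via the" Mann-Whitney *U* test, again with no outcome named;
- ANCOVA for the primary outcome at baseline, day 5 and day 10;
- longitudinal regression for the effect of the intervention.

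The adjusted analyses are said to cover zonulin. Their covariates are age, sex, BMI, APACHE II, diagnosis category, vasopressor use and comorbidity groups. Baseline zonulin is not among them. One rule covers everything: "Statistical significance will be set at p < 0.05".

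**The concern.** The sample size assumes one between-arm test at 0.05. The analysis section does not contain that test and offers several others for the same outcome at the same threshold. The 5% error rate therefore belongs to no identified result, and a reader of the final report could not tell whether the headline test was chosen before or after the data were seen.

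The paired test raises a different problem. Zonulin may move over ten ICU days in both arms through recovery or regression to the mean. A test of day 10 against day 0 within an arm asks whether zonulin moved, not whether HP differs from CP. Significance in one arm and not in the other is not evidence of a treatment effect. The Discussion says that a significant fall in zonulin together with better clinical outcomes could influence guidelines, so which comparison supports that statement matters.

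**Working it through.** **1. The plan's own figure.** Inputs from section 2.9: the mean zonulin "was reported to be 3.40 ng/mL, with a standard deviation of 0.71", a 10% difference, two-sided alpha 0.05 and power 80%.

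- Difference: 0.10 × 3.40 = 0.34 ng/mL.
- n per group = 2(1.960 + 0.842)² × 0.71² / 0.34² = 68.5, so 69 (70 with the exact *t*).
- The plan states 41, which does not reproduce. The attrition step does: 41 / 0.95 = 43.2, so 44.

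The shortfall from 69 to 41 is a separate matter and does not drive this point. What matters here is that the planning calculation is for one unadjusted between-arm test.

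**2. Which analyses reach zonulin.** ANCOVA is tied by name to the primary outcome, and longitudinal regression to the intervention effect. The paired and Mann-Whitney sentences are generic, so applying them to zonulin is an inference. It is a reasonable one. Section 2.1 schedules only zonulin and SOFA more than once, and section 2.8 says APACHE II and mNUTRIC are scored only at admission. Among the named outcomes and scores, only zonulin and SOFA can be pre/post measures. Zonulin is also continuous.

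**3. False-positive rate if any significant between-arm test counts.** The documents give no figure, so this is a simulation with no arm difference. Assumptions: 44 per arm, normal data, SD 0.71, equal correlation between days, ten noise covariates plus baseline zonulin in the ANCOVA, and a longitudinal contrast equal to the mean of days 5 and 10. There were 3,000 runs per scenario. Results with no time trend:

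| Assumed correlation | ANCOVA day 5 or 10 | + longitudinal contrast | + Mann-Whitney at both days |
|---|---|---|---|
| 0.3 | 0.088 | 0.100 | 0.138 |
| 0.5 | 0.093 | 0.103 | 0.147 |
| 0.7 | 0.095 | 0.103 | 0.160 |
| 0.9 | 0.082 | 0.090 | 0.148 |

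Adding a time change common to both arms (-0.15 or -0.30 ng/mL), the ranges over all scenarios are 0.08-0.11, 0.09-0.12 and 0.14-0.17. Monte Carlo error near 0.10 is √(0.10 × 0.90 / 3000) = 0.005. For independent tests the rate would be 1 - 0.95^k: 0.0975 for two, 0.143 for three and 0.226 for five. The simulated rates for three and five tests are lower because the tests are correlated. A single pre-named test, ANCOVA at day 10, gave 0.044-0.055.

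**4. Paired tests within arms.** Assume both arms fall equally by *d* SD, with correlation 0.5 and 41 per arm. The SD of the within-patient change is √(2(1 - 0.5)) = 1 SD, so the noncentrality is *d*√41. With *p* the power of the paired test in one arm, exactly one arm is significant with probability 2*p*(1 - *p*).

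| Fall (SD) | Noncentrality | *p* | 2*p*(1 - *p*) |
|---|---|---|---|
| 0.2 | 1.28 | 0.240 | 0.364 |
| 0.3 | 1.92 | 0.466 | 0.498 |
| 0.4 | 2.56 | 0.705 | 0.416 |

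This probability does not rise steadily with the size of the fall. In the simulation (44 per arm) it was 0.09-0.10 with no time change, peaked at 0.49, and was zero at correlation 0.9 with a fall of 0.30 ng/mL, where both arms were always significant.

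**The case against.** The strongest reply has four parts.

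- **The sentences are generic.** Mann-Whitney may be a fallback after the Kolmogorov-Smirnov check, not an extra test, and the paired test is nowhere described as within-arm. This stands as a caution: both uses are readings. The text does not state the fallback, however, and a fallback would choose the test after the data are seen.
- **ANCOVA may be one repeated-measures model.** This also stands. The two-day figure would then not apply and the rates would be lower. Mann-Whitney and the longitudinal model would still compete with it.
- **Ranking of analyses is commonly left to an SAP, and this is a condensed article.** Silence alone would not be a finding. But the article is not silent: it sets out overlapping analyses, and none matches its own planning test.
- **The outcome is called exploratory.** That softens the concern. Zonulin is still the named primary outcome and the basis of the sample size.

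A reader might infer that the trial's false-positive rate is two to three times 5%, with the paired tests included in that count. The documents do not support this. No rule says that any significant result is success, the correlations are assumed, and the upper end needs Mann-Whitney to run beside ANCOVA at both days. The between-arm figures also exclude the paired tests, whose fault is the wrong comparison and not multiplicity. Nor does the protocol say that significance in one arm only would be read as an effect.

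**Conclusion.** The point holds in limited form. Section 2.10.16 sets out overlapping analyses of the primary outcome at one threshold, and none is the test on which section 2.9 rests. The cost is conditional: about 0.08-0.12 for ANCOVA at two days with or without a longitudinal contrast, and about 0.14-0.17 if Mann-Whitney is added at both days. Both ranges require that any significant between-arm result be taken as success, and both rest on normal data and assumed correlations of 0.3-0.9.

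The paired *t*-test, read as within-arm, cannot answer the primary question whatever its p-value. The 36-50% figure illustrates this under assumed equal falls and correlation 0.5; it does not predict what this trial will show. The matter should be corrected, and the Trial registration section says recruitment has not begun.

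**What to change.** Before recruitment, amend section 2.10.16 and align section 2.10.4 and the abstract with it:

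- Name one primary between-arm contrast at two-sided 0.05, from a model that includes baseline zonulin as a covariate. Two defensible choices are the HP-CP difference at day 10 from the longitudinal model using days 5 and 10, or the average difference over both days. The abstract's wording, change over the intervention period, does not settle which.
- Drop the comparison at baseline as an outcome test. Under randomisation a baseline difference arises by chance.
- Label the other between-arm tests, Mann-Whitney included, as supportive.
- Restrict pre/post paired comparisons to description without inference.
- If both days are to stay primary, test each at 0.025 (Bonferroni), which holds the total at or below 0.05.

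The cost is wording only. The downside is that an effect seen only on the other day or in another test becomes supportive. If day 10 is chosen, discharge and death before day 10 reduce the available samples; section 2.10.8 has feeding end at ICU discharge or day 10.

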**Methods:**

Participants were selected from 88 adult patients with critical illness aged 18-65 years who were admitted to the ICU of Hazrat Rasoul Akram Hospital in Tehran. In this randomized controlled clinical trial, patients will be allocated randomly into two groups of 44. The intervention group will receive high-protein (HP) enteral nutrition (1.6 g/kg/day), and the control group will receive conventional-protein (CP) enteral nutrition (1.2 g/kg/day) for 10 days. The primary outcome will be the change in serum Zonulin levels during the intervention period. Zonulin will be measured on days 0, 5, and 10. The SOFA, APACHE II, and mNUTRIC scores will also be assessed. Mortality will be calculated at 30 and 60 days after the intervention. The secondary outcomes will be SOFA score and 30- and 60-day mortality.

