#### Confounding variables

2.10.6

Potential confounding variables include age, sex, BMI, APACHE II score at ICU admission, admission diagnosis category, vasopressor use during the intervention, and underlying comorbidities. Comorbidities will be categorized into predefined clinical groups, including Trauma, cancer, surgery, diabetes mellitus, kidney disease, cardiovascular disease, and liver disease. These factors should be measured and considered, as they may influence outcomes.

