#### Zonulin

2.10.11

Zonulin levels will be measured in blood samples. Blood samples (5 ml) will be taken from patients before the intervention and again on days 5 and 10 to measure zonulin levels. After centrifugation, the serum will be separated. Zonulin levels in the serum sample will be measured via a sandwich ELISA. The method involves incubating a sample with a specific antibody against zonulin, followed by subsequent detection of the bound zonulin using a secondary antibody and a colorimetric substrate.

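### The zonulin ANCOVA lists baseline as a compared time point and does not name day-0 zonulin as a covariate, which costs precision but does not bias the comparison

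*Protocol article*

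**What the plan says.** The abstract defines the endpoint: "The primary outcome will be the change in serum Zonulin levels during the intervention period". The Zonulin section (2.10.11) sets the sampling times: "Blood samples (5 ml) will be taken from patients before the intervention and again on days 5 and 10". Day 0 is therefore a pre-treatment value.

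The Statistical analysis section (2.10.16) gives the method: "ANCOVA will compare primary outcomes at baseline, day 5, and day 10". It then names the covariates for the multivariable regression and ANCOVA models: "Potential confounders including age, sex, BMI, APACHE II score at ICU admission, admission diagnosis category, vasopressor use during the intervention, and predefined comorbidity groups". The longitudinal models take the same set: "Longitudinal regression models will assess the intervention's effect, controlling for the same confounding factors". The Confounding variables section (2.10.6) gives a matching list: "Potential confounding variables include age, sex, BMI, APACHE II score at ICU admission, admission diagnosis category, vasopressor use during the intervention, and underlying comorbidities". Day-0 zonulin appears in neither list, and no other section names it as a covariate.

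**The concern.** Two things look wrong when these sentences are read together.

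- **Baseline sits with the outcomes.** Protein dose cannot influence a sample taken before the intervention. A between-group comparison at day 0 can only show chance imbalance and says nothing about the treatment.
- **Baseline is missing from the covariates.** When an outcome is measured before and after treatment, its baseline value is normally included to remove chance imbalance and reduce residual variance. Here the protocol names seven kinds of covariate and leaves this one out, although the endpoint is a change from it.

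The stake is precision in the primary analysis. It matters here because the planned sample gives less power than the protocol states (see the working). An unstated option to add baseline also leaves the primary model open to choice after the data are seen.

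**Working it through.** **Inputs.** From the Sample size section (2.9): mean 3.40 ng/mL, SD 0.71, relevant change 10%, two-sided α 0.05, power 80%, independent-samples t-test, 41 per group, raised to 44 for 5% attrition. The difference is 0.10 × 3.40 = 0.34 ng/mL and the standardised effect is 0.34 / 0.71 = 0.479. The correlation ρ between day-0 and follow-up zonulin is not in the document, so it is varied.

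**The protocol's own figure.** n per group = 2 × [SD × (1.960 + 0.842) / δ]² = 2 × [0.71 × 2.802 / 0.34]² = 68.4, so 69 (70 with the exact t distribution). The stated 41 is not reproduced. The attrition step is correct: 41 / 0.95 = 43.2, so 44. With 41 per group, power for 0.34 ng/mL is 57% (exact t; 58% by normal approximation).

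**Effect of adding day-0 zonulin.** The residual SD becomes 0.71 × √(1 − ρ²), so the standardised effect becomes 0.479 / √(1 − ρ²). Exact t power at 41 per group:

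| ρ (assumed) | Residual variance removed (ρ²) | Standardised effect | Power |
|---|---|---|---|
| 0 | 0% | 0.479 | 57% |
| 0.3 | 9% | 0.502 | 61% |
| 0.5 | 25% | 0.553 | 70% |
| 0.6 | 36% | 0.599 | 76% |
| 0.7 | 49% | 0.671 | 85% |

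**Where adjustment alone would reach 80%.** By normal approximation, 41 per group suffices when 68.4 × (1 − ρ²) ≤ 41, that is ρ ≥ √(1 − 41/68.4) = 0.63. Below that, adjustment helps but does not restore the planned power.

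**Unadjusted change score, for comparison.** Its SD is 0.71 × √[2(1 − ρ)]. At 42 evaluable per group (about 44 × 0.95, normal approximation), power is 46%, 59% and 81% at ρ 0.3, 0.5 and 0.7. The baseline-adjusted ANCOVA gives 63%, 72% and 87%. Analysing raw change is therefore no substitute for the covariate.

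**The case against.** The strongest reply is that the text is loose rather than wrong. The covariate list is introduced as a list of potential confounders and is not closed. A baseline outcome value is usually a precision covariate, so its absence from a confounder list need not mean exclusion. ANCOVA on a pre/post outcome commonly implies baseline adjustment, and the comparison at the three times could mean a repeated-measures comparison across visits. This stands as a statement of what may be intended. It does not change what an analyst following the text would do: the covariates are named without baseline, and baseline is placed among the compared times.

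Three stronger readings are tempting, and the document does not support them:

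- **That the effect is diluted.** If one group effect were averaged over days 0, 5 and 10, a constant post-baseline effect δ would shrink to (0 + δ + δ)/3 = two thirds of δ. But the protocol does not say that day 0 is in the longitudinal outcome vector, nor that one averaged effect is used. A group-by-time contrast would not be diluted.
- **That change is not estimated.** A group-by-time term estimates a difference in change, and the longitudinal model is not specified closely enough to rule it out.
- **That day-0 zonulin is the strongest available predictor.** No correlation is given, so this cannot be asserted.

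Two further objections stand. The 57% comparator is an unadjusted t-test, whereas the plan already adjusts for other factors; where those share variance with baseline zonulin, the extra gain is smaller. And in a randomised trial, leaving baseline out does not bias the treatment estimate.

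**Conclusion.** The point holds as a wording fault in the primary analysis with a cost in precision. As written, the ANCOVA includes a day-0 comparison that cannot reflect treatment, and day-0 zonulin is not a named covariate in any model. Validity is not affected.

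Relative to an unadjusted test at 41 per group, the power forgone is about 4 percentage points at ρ 0.3, 12 at 0.5, 19 at 0.6 and 28 at 0.7. These figures rest on the protocol's SD of 0.71 and difference of 0.34 ng/mL, on an assumed ρ, and on a comparator without the other covariates. Confidence is high on the wording and low on the exact gain.

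A reader might infer that this omission explains the low power, or that correcting it repairs the sample size. Neither follows. The shortfall comes from the calculation in section 2.9, which gives 69 to 70 per group on its own inputs and needs separate correction.

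**What to change.** - Name day-0 zonulin as a covariate in the ANCOVA and longitudinal models, in sections 2.10.6 and 2.10.16.
- Remove baseline from the outcome time points at which the groups are compared.
- Define the treatment contrast (high-protein minus conventional-protein) on the post-baseline values at days 5 and 10, and have the investigators state which of these is primary.
- If day 0 is kept in the longitudinal outcome vector, use a group-by-time contrast with a common baseline mean, not one group effect averaged over all visits.

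**Cost.** No new data are needed, because day-0 zonulin is already scheduled, and the protocol states that recruitment has not begun. Adding the covariate and removing baseline from the compared times are changes of wording. Choosing the primary post-baseline time point is a substantive decision that the protocol has not yet made, and it should be settled before enrolment starts.
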